## Abstract

Fatigue’s interference with activities, mood, and cognition is one of the most prevalent and distressing problems of patients with advanced gastrointestinal cancer. As fatigue interferes with patient functioning, family caregivers often report feeling burdened by increasing demands. Evidence-based interventions for patient fatigue interference and caregiver burden are lacking in advanced gastrointestinal cancer. In a pilot trial, telephone-based Acceptance and Commitment Therapy (ACT) showed potential for reducing patient fatigue interference and caregiver burden in this population. The current Phase II trial seeks to determine the efficacy of this intervention for patients with advanced gastrointestinal cancer and moderate-to-severe fatigue interference and their family caregivers with significant caregiving burden. In this trial, 244 dyads are randomly assigned to either the ACT intervention or an education/support control. Participants in both conditions attend six weekly 50-min telephone sessions, four of which involve both dyad members, and a 30-min booster session. The primary aim is to test the effects of telephone-delivered ACT on patient fatigue interference and caregiver burden. Secondary outcomes include patient sleep interference and patient and caregiver engagement in daily activities and quality of life. Outcomes are assessed at baseline, 2 weeks post-intervention, and 3 months post-intervention. This trial also examines whether increased psychological flexibility, defined as mindful acceptance of present experiences, including challenges, while pursuing actions aligned with personal values, mediates ACT’s effects on primary outcomes. Our ability to demonstrate ACT’s efficacy will support its adoption in cancer care. Findings will also inform future ACT trials for dyads coping with other serious illnesses.

## Introduction

1.

Fatigue is a prevalent, disabling symptom in patients with advanced gastrointestinal (GI) cancer [1–4]. Moderate-to-severe fatigue is reported by up to 68 % of patients with metastatic colorectal cancer [1,2]. Among patients with GI cancer, fatigue has been associated with impaired daily activities and other symptoms [1,5–8]. As symptoms interfere with patient functioning, family caregivers face increased demands that affect their quality of life (QoL) [9–11]. Among caregivers of patients with colorectal cancer, greater caregiving burden, defined as the impact of caregiving on various aspects of their lives, has been associated with worse QoL [12]. As colorectal cancer incidence increases among younger adults [13], their caregivers often experience significant stressors, including balancing multiple roles and heightened economic strain [14,15].

Evidence-based interventions for addressing patient fatigue and caregiver burden in advanced cancer are lacking. Meta-analyses of pharmacologic and behavioral interventions for fatigue in advanced cancer characterized the evidence as inconclusive and highlighted the small samples in many studies [16,17]. Additionally, behavioral interventions for cancer caregivers have produced small effects on caregiving burden and QoL [18,19]. Meta-analytic findings suggest that psychotherapy and skills training interventions show greater promise for decreasing cancer caregiver burden than psycho-education/support interventions [19]. Most of these intervention trials did not focus on caregivers of late-stage patients and did not have a distress criterion for eligibility. Thus, effect sizes may have been larger if the trials had focused on subgroups most in need of intervention.

One behavioral intervention with strong potential for reducing cancer patient and caregiver suffering is acceptance and commitment therapy (ACT) [20,21]. Rather than aiming to reduce symptoms, the goal of ACT is to increase psychological flexibility so that unwanted internal experiences (e.g., symptoms, feelings, thoughts) interfere less with valued activities [22,23]. Psychological flexibility is a multidimensional construct comprised of mindfulness/acceptance processes (i. e., nonjudgmental attention to the present moment) and commitment/behavior change processes (i.e., identifying personal values and taking action steps aligned with these values) [22,23]. ACT has shown evidence of feasibility and acceptability in pilot trials with patients and patient-caregiver dyads coping with advanced cancer [21,24–26]. In our pilot RCT, 40 advanced GI cancer patient-caregiver dyads were randomized to six telephone sessions of either ACT or time-equivalent education/support [21]. ACT showed strong evidence of feasibility and promise in reducing patient fatigue interference with functioning and caregiver burden. Feasibility was demonstrated by the eligibility screening rate (54 % of reached patients and 96 % of reached, patient-identified caregivers agreed to be screened), consent rate (100 % of eligible patients and caregivers consented), and retention (81 % of participants at 2 weeks post-intervention and 73 % at 3 months post-intervention). Most attrition (82 %) was due to severe medical problems or death.

The primary aim of this NIH-funded Phase II RCT is to examine the efficacy of our telephone-delivered ACT intervention for patients with advanced GI cancer and fatigue interference and their family caregivers with caregiver burden. We hypothesize that ACT will lead to improved primary outcomes of patient fatigue interference and caregiver burden compared to time-matched education/support. Our second aim is to examine ACT’s effects on the secondary outcomes of patient sleep interference and patient and caregiver engagement in daily activities and QoL. We hypothesize that ACT will lead to improved secondary outcomes compared to education/support. Our third aim is to test the hypothesis that increased psychological flexibility will mediate ACT’s effects on patient fatigue interference and caregiver burden. Our fourth aim is to explore changes in the two core aspects of psychological flexibility (i.e., mindfulness/acceptance and commitment/behavior change processes) as mediators of ACT’s effects on patient fatigue interference and caregiver burden. This paper describes the rationale, study design, methods, and statistical plan.

## Materials and methods

2.

### Overview of study design

2.1.

This Phase II RCT tests the effects of telephone-based ACT on patient fatigue interference and caregiver burden in advanced GI cancer. We plan to enroll 244 patient-caregiver dyads over about four years. Dyads are randomized to six weekly 50-min telephone sessions of ACT or six weekly 50-min telephone sessions of education/support. Outcomes are assessed at baseline, 2 weeks post-intervention, and 3 months post-intervention (primary endpoint). Dyads in both conditions also complete a 30-min booster phone session one month after the 2-week follow-up. This trial is registered in clinicaltrials.gov (NCT06532877) and approved by the Indiana University Institutional Review Board.

### Participant eligibility criteria

2.2.

To enroll in this study, both the patient and caregiver need to be eligible and consent to participate. Patient eligibility criteria are as follows: a) unresectable stage III or IV GI cancer according to medical records and the oncologist, b) no significant cognitive impairment as ascertained by medical records and a mental status questionnaire (<3 errors) [27], c) in bed or chair less than half the day (patient-reported Eastern Cooperative Oncology Group [ECOG] score ≤ 2) [28], d) not enrolled in hospice, e) has an eligible, consenting family caregiver, and f) elevated fatigue interference (mean score ≥ 2.5 on the Fatigue Interference subscale of the Fatigue Symptom Inventory [FSI]) [29,30]. In our pilot research in advanced cancer, this level of fatigue interference was significantly associated with clinically meaningful fatigue (score ≥ 3 on the FSI composite measure) [31]. Caregiver eligibility criteria are as follows: a) family or friend caregiver who either lives with the patient or has visited them at least twice a week for the past month, and b) significant caregiving burden (score ≥ 4 on the 4-item Zarit Burden Interview, score ≥ 6 on the 6-item Zarit Burden Interview, or score ≥ 7 on the 7-item Zarit Burden Interview [32]). Clinical cutoffs on the caregiving burden measures have been established in advanced cancer caregivers [32]. Other patient and caregiver eligibility criteria are: a) ≥18 years of age, b) English fluency, c) working phone service, and d) no hearing impairment that precludes study participation.

### Recruitment

2.3.

Potentially eligible patients are identified via medical record review and consultation with the oncologist. Patients receive recruitment materials and a consent form via the hospital’s email system or postal mail. Materials include contact information for those who have questions or wish to opt out.

Study staff call patients who do not opt out at least 3 days after emailing the recruitment materials or about 1 to 2 weeks after mailing the materials. The staff member describes the study as testing telephone support programs for stress and symptoms and answers questions. Then the staff member administers a screening assessment (i.e., identification of caregiver, Fatigue Interference subscale of FSI [29,30], ECOG [28], and mental status questionnaire [27]) with the patient’s permission. Eligible and interested patients provide verbal consent for study participation over the phone. Caregivers of consenting patients receive recruitment materials via email or postal mail followed by telephone calls for eligibility screening and consent. Other patients and caregivers are approached during an oncology clinic visit for eligibility screening and written informed consent.

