### Study measures and data collection schedule

2.7.

Study measures and the data collection schedule are shown in Table 2. REDCap is used to store study data. Patients and caregivers individually complete a 35-min baseline assessment and two, 30-min follow-up assessments conducted by blinded staff. All outcomes and mediators have evidence of internal consistency reliability and construct validity in cancer, general population, or caregiving samples [3,29,30,32,47–56].

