#### Primary outcomes

2.7.1.

The primary outcome measure for patients is the 7-item Fatigue Interference subscale of the FSI [29,30]. Items evaluate the extent to which fatigue in the past week interfered with activities, mood, and cognition on 11-point scales (0 = no interference; 10 = extreme interference). The primary outcome measure for caregivers is the 12-item Zarit Burden Interview [32,47], which assesses personal strain and role strain due to caregiving on 5-point scales (0 = never; 4 = nearly always).

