#### Analyses of potential covariates

3.1.2.

*T*-tests and chi-square analyses will be used to examine differences between study conditions on potential baseline covariates (e.g., demographics, medical factors). Any differences will be considered when interpreting results, and factors that differ between groups will be included as covariates in sensitivity analyses.

### Analysis for aim 1

3.2.

Linear mixed effects modeling (R lme4) [66] will be used to test the hypothesis that ACT will improve the primary outcomes of patient fatigue interference and caregiver burden as compared to education/support. The model for each outcome will include the main effects of time (as categorical) and condition (ACT vs. education/support) and the time-by-condition interaction. Time will be dummy coded using two dummy variables, with baseline as the reference group. A treatment effect will be evidenced by a significant time-by-condition interaction. If the treatment effect is significant, follow-up tests (R emmeans) [67] will be performed to examine group differences at each follow-up.

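### The patient's screening FSI interference score, a second pre-randomization measurement of the patient primary outcome, is not used in the Aim 1 model

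*Protocol article*

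**What the plan says.** Protocol article, 2.3 (Recruitment): during the screening call the staff member "administers a screening assessment (i.e., identification of caregiver, Fatigue Interference subscale of FSI [29,30". Section 2.2 sets the entry rule on that subscale: "elevated fatigue interference (mean score ≥ 2.5 on the Fatigue Interference subscale of the Fatigue Symptom Inventory [FSI". Section 2.7.1 makes it the patient endpoint: "The primary outcome measure for patients is the 7-item Fatigue Interference subscale of the FSI".

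Section 2.7 describes a separate baseline session: "Patients and caregivers individually complete a 35-min baseline assessment and two, 30-min follow-up assessments conducted by blinded staff". Table 2 lists the FSI interference subscale at baseline and at both follow-ups. Section 2.4 places randomization after baseline.

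The primary model is set out term by term in 3.2: "The model for each outcome will include the main effects of time (as categorical) and condition", plus the time-by-condition interaction, with baseline as the reference level of time. Baseline is therefore a response in the model, not a covariate. If the interaction is significant, emmeans comparisons of the groups at each follow-up are planned. Under 3.1.2, covariates enter only sensitivity analyses, chosen because they differ between groups. No described analysis uses the screening score.

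Caregivers are different. They enter on "score ≥ 4 on the 4-item Zarit Burden Interview, score ≥ 6 on the 6-item Zarit Burden Interview, or score ≥ 7" on the 7-item form, whereas "The primary outcome measure for caregivers is the 12-item Zarit Burden Interview".

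**The concern.** A single self-report score is a noisy measure of a person's usual level. Patients are also selected for a high value at screening, which weakens the correlation of the baseline score with later scores. A second score on the same subscale, taken before randomization, carries some further information about the 3-month score and can be adjusted for without biasing the comparison. The plan uses it only as an entry gate.

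What is at stake is precision for the patient primary outcome, in a trial that expects 30% attrition by 3 months and whose stated power already relies on some gain from repeated measurement.

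**Working it through.** **Inputs from the article (2.2, 3.2).** d = −0.40; 170 dyads at 3 months, so 85 per arm; two-tailed α = 0.05; stated power 85%; entry cutoff 2.5.

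**Assumed, because the article gives none.** Correlations before selection: p = 0.6 to 0.85 between screening and baseline, r = 0.5 to 0.6 of each with 3 months. Scores have SD 2.4 and mean 3 or 4, are clipped to 0–10, and are truncated at screening ≥ 2.5.

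**Step 1: the stated power.** A plain two-sided comparison gives Φ(0.40 × √(85/2) − 1.960) = Φ(2.608 − 1.960) = 74.1%. Reaching 85% needs a variance factor of (2.608 / (1.960 + 1.036))² = 0.757. A baseline-adjusted analysis has factor 1 − r², which gives r = 0.49. A change-from-baseline contrast has factor 2(1 − r), which gives r = 0.62. So 85% is attainable but rests on a within-person correlation that the article does not state.

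**Step 2: what the screening score removes, before truncation (unit variance, complete data).**
- Time-by-condition contrast (in effect, change from baseline): variance 2(1 − r); fraction removed (p − r)² / [2(1 − r)]. At p = 0.7, r = 0.5: 0.04 / 1 = 4%. At p = r = 0.6: 0.
- Baseline-adjusted analysis: 1 − r² falls to 1 − 2r²/(1 + p). At p = 0.7, r = 0.5: 0.750 to 0.706, a fall of 5.9%.
- Group difference at 3 months with no baseline adjustment: 1 falls to 1 − r². At r = 0.5: 25%.

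**Step 3: with truncation at 2.5 (simulation).** Variance removed by the screening score:

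| p / r before selection | Planned time-by-condition contrast | Beyond a baseline-adjusted analysis |
|---|---|---|
| 0.6 / 0.6 | 0.0% | 8–9% |
| 0.6 / 0.5 | about 0.5% | about 5% |
| 0.7 / 0.5 | about 2% | about 4% |
| 0.85 / 0.5 | 6–7% | 2% |

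The two columns run in opposite directions. The change contrast gains only when screening predicts baseline better than it predicts 3 months.

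For the planned 3-month emmeans difference, the screening score removes about 12 to 23%. Baseline adjustment would do much the same. In a companion simulation (SD 2.3, mean 3.0 or 4.5), truncation left screening-to-3-month correlations of 0.346 to 0.499, whose squares are 12.0% and 24.9%. The baseline-to-3-month correlations were 0.362 to 0.508, whose squares are 13.1% and 25.8%. Once baseline was adjusted for, adding screening removed 2.4 to 5.1% of what remained, worth 0.9 to 1.7 power points.

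**Step 4: the form of the term matters.** In one simulated complete data set of 170 dyads (p = 0.7, r = 0.5), the SE of the 3-month interaction was:
- planned model: 0.1441;
- with screening as a main effect: 0.1441, and the estimate (−0.368) was unchanged;
- with screening by visit: 0.1420.

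The main effect does nothing because the score is constant over a patient's visits and cancels from the change. Simulating the random-intercept model with 244 dyads and 30% missing at 3 months, screening by visit lowered the SE by 0.5% (p/r = 0.6/0.6), 1.0% (0.7/0.5) and 3.6% (0.85/0.5).

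**The case against.** The strongest reply is that nothing here is wrong. The model in 3.2 is valid, an extra precision covariate is optional, and the full protocol or analysis plan, not shown, may already include it. That stands as far as it goes: this is an improvement, not a correction. But the article states the primary model term by term and confines covariates to sensitivity analyses, so the suggestion bears on a stated model.

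A reader might infer that both primary outcomes are measured twice before randomization. The article does not support that. The 12-item Zarit is scheduled once before randomization; screening is described only with 4-, 6- or 7-item forms, which are at most a correlated proxy.

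A reader might also expect 1 to 3 more power points, or the equivalent of 4 to 17 extra dyads. Those figures belong to a baseline-adjusted analysis, which 3.2 does not specify. For the planned contrast the gain can be nil, as at 0.6/0.6.

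Two further cautions stand. The article does not give the interval between screening and baseline. Some participants are screened at a clinic visit and the FSI asks about the past week, so the two recall periods may overlap. Nor does it say outright that the FSI is asked again at baseline and not carried forward, although the separate sessions and Table 2 imply that it is.

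**Conclusion.** The point holds for the patient outcome only, as a minor and optional gain in precision. The FSI interference subscale is collected at screening and scheduled again at baseline, both before randomization, and the Aim 1 model ignores the screening score.

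The size depends on the contrast: about 0 to 7% of variance for the planned time-by-condition test, about 2 to 10% beyond a baseline-adjusted analysis, and about 12 to 23% for the planned 3-month group difference. The last figure is large mainly because the stated model makes no baseline adjustment, and adjusting for baseline would capture most of it. All three ranges rest on assumed correlations, SD and means, and on the FSI being asked afresh at baseline.

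It would be wrong to read this as bias, as an invalid analysis, or as proof that the 85% power is false.

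**What to change.** In 3.2, prespecify the screening FSI interference score and its interaction with visit as a covariate in the patient primary model. Do not enter it as a main effect alone. First confirm that the subscale is asked again at baseline; where it is carried forward the gain disappears, and where both fall on the same day it is small.

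The cost is one main effect and two visit-interaction terms, from data already collected for every enrolled patient, with no added burden on participants.

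For caregivers, a screening Zarit score could be used in the same way as an optional extension. One common short form would have to be named first, and the gain has not been computed.

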### Randomization and blinding

2.4.

Following baseline assessments, dyads are randomly assigned to ACT or education/support using stratified block randomization to balance the groups by patient age (<65 yrs. vs. ≥65 yrs.) and performance status (patient-reported ECOG scores 0 or 1 vs. 2 [28]). Performance status informs treatment decisions for advanced GI cancer [33]. The statistician uses the R package “blockrand” [34] to generate random assignments within blocks. Randomly varying block sizes of 2 and 4 are used to maintain allocation concealment and ensure balanced allocation to study conditions. Following randomization, study condition assignments are identifiable to participants, interventionists, their supervisors, and staff mailing intervention materials. Other investigators, outcome assessors, and data analysts are blinded.

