#### Missing data/attrition

3.1.1.

We will examine demographic and medical factors at baseline that might predict dropout using logistic regression. For Aims 1 and 2 described below, all randomized participants will be included in intent-to-treat analyses [65]. Second, for participants who miss assessments, we will use full information maximum likelihood (FIML) to handle missing data without disregarding any incomplete cases.

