Linear mixed effects modeling (R lme4) [66] will be used to test the hypothesis that ACT will improve secondary outcomes as compared to education/support. For outcome measures that only patients or caregivers complete, models will include main effects of time (as categorical) and condition and the time-by-condition interaction. Treatment effects will be evidenced by a significant time-by-condition interaction. For outcomes reported by patients and caregivers, multilevel modeling for dyadic data will be used [77,78]. The model will include the main effects of time, condition, and social role (patient vs. caregiver) as well as all two and three-way interactions. The time x condition x role interaction will estimate the degree to which the treatment effect is different for patients and caregivers. The *p* values from the analyses will be adjusted using the Sidak approach to control for the familywise Type I error rate due to correlated multiple secondary outcomes. If treatment effects are significant, follow-up tests (R emmeans) [67] will be performed to examine group differences at each follow-up.

### Analysis for aim 3

3.4.

Cross-lagged panel models in Mplus [79] will be used to test the hypothesis that increases in psychological flexibility will mediate ACT’s effects on primary outcomes (patient fatigue interference and caregiver burden). Outcomes will be examined in separate models that include condition, the mediator (assessed at baseline and 2 weeks post-intervention), and the outcome at all time points. To evaluate model fit, we will use the comparative fit index (CFI) and the root mean square error of approximation (RMSEA), with CFI ≥0.95 and RMSEA ≤0.05 indicating close fit [80]. The indirect effect of condition on each outcome via psychological flexibility will be quantified using the product of the two relevant effects and tested using bootstrapped confidence intervals (CIs) accounting for nonnormality [81]. A total of 10,000 bootstrapped samples will be drawn, and the indirect effect will be considered statistically significant at *p* < .05 if the 95 % CI does not include zero.

### Analysis for aim 4

3.5.

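### Age and performance-status strata are used to randomize but are absent from the Aim 1 and Aim 2 models, and the covariate rule is unlikely to admit them; adding them with time interactions is a cheap, modest gain

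*Protocol article*

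**What the plan says.** Section 2.4 of the protocol article describes "stratified block randomization to balance the groups by patient age" (under 65 against 65 and over) and by "performance status (patient-reported ECOG scores 0 or 1 vs. 2". Of the blocks it says: "Randomly varying block sizes of 2 and 4 are used".

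Section 3.2 lists the primary model terms: "The model for each outcome will include the main effects of time (as categorical) and condition (ACT vs. education/support) and the time-by-condition interaction". Baseline is the reference time, and the test is stated directly: "A treatment effect will be evidenced by a significant time-by-condition interaction". In section 3.3, for outcomes that only patients or only caregivers report, "models will include main effects of time (as categorical) and condition and the time-by-condition interaction". For outcomes that both report, social role and its interactions are added. Neither age group nor ECOG group appears in any of these lists.

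Section 3.1.2 gives the only stated rule for covariates: baseline factors found to differ between conditions enter sensitivity analyses. Section 3.1.1 handles missed assessments by full information maximum likelihood and adds: "We will examine demographic and medical factors at baseline that might predict dropout using logistic regression". The Introduction reports that 82% of pilot attrition was due to severe medical problems or death, and section 3.2 plans for 30% attrition.

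**The concern.** An analysis normally reflects the way patients were randomized. Here the covariate rule works against that. It selects factors by observed imbalance, and age group and ECOG group are the two factors the design forces towards balance. As written, they are unlikely to enter even a sensitivity analysis.

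Two things could be at stake. The first is precision: if a balanced factor predicts the tested contrast, leaving it out keeps explainable variance in the standard error, so the test is conservative and some power is lost. The second is missing data: a likelihood analysis is valid under missing-at-random only given the variables in the model. When attrition is largely medical, performance status is a plausible link between dropout and the course of fatigue interference, although the documents do not say that it predicts either.

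**Working it through.** **The plan's own figure.** Inputs from sections 2.1 and 3.2: 244 dyads, 30% attrition, d = 0.40, two-sided alpha 0.05, stated power 85%. 244 × 0.70 = 170.8, so 170 dyads, or 85 per arm (1:1 is implied by the block sizes). Power ≈ Φ(d√(n/2)/SD − 1.96).

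- Follow-up score alone, SD = 1: 0.40 × √42.5 = 2.608; Φ(0.648) = 74.1%.
- Adjusted for baseline, r = 0.5, SD = √0.75: 2.608/0.866 = 3.01; power 85.3%.
- Change from baseline, SD = √(2(1 − r)): 74.1% at r = 0.5 and 83.0% at r = 0.6.

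The stated 85% fits an unprinted correlation and cannot be confirmed. The present point does not depend on it.

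**What the planned test can gain.** Suppose stratum s shifts the mean by a at baseline and by a + c at 3 months. The time-by-condition contrast is a difference in changes, so a cancels and only c matters. The relevant quantity is therefore the share R² of the variance of *change* that the strata explain. The documents do not give it.

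Take a completer change contrast with r = 0.5 (SD = 1) and replace SD by √(1 − R²). Power then goes from 74.1% to 75.0% (R² = 2%), 76.3% (5%) or 78.5% (10%). The unadjusted test would have true size 2(1 − Φ(1.96/√(1 − R²))): 4.4% at R² = 5% and 3.9% at 10%. These R² values are assumptions.

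**Simulation of the planned contrast.** 800 runs per scenario, 244 dyads, random-intercept model fitted by REML, 3-month time-by-condition term. All inputs below are assumptions:

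- intraclass correlation 0.5; 30% with ECOG 2; 45% aged 65 or over;
- stratum effects on level of 0.5 SD (ECOG) and 0.25 SD (age);
- where strata also affect change, the same amounts again by 3 months. That explains (0.25 × 0.21 + 0.0625 × 0.2475)/(1 + 0.068) = 6.4% of the variance of change;
- dropout before the two follow-ups of 12% then 8%, with 14 then 12 points more for ECOG 2, so overall 0.7 × 19.0% + 0.3 × 40.8% = 25.6%;
- in the differential case, a further 20 points per interval for ECOG 2 in the ACT arm only. ECOG-2 dropout is then 1 − 0.54 × 0.60 = 67.6% against 40.8%, and overall dropout is 29.6%.

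Each cell gives estimate / mean model SE / rejection rate; a positive estimate favours ACT.

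| Scenario | No strata | Strata main effects | Strata × time |
|---|---|---|---|
| No effect; level only; equal dropout | −0.002 / 0.143 / 4.0% | −0.001 / 0.143 / 4.0% | −0.001 / 0.143 / 3.7% |
| No effect; level and change; equal dropout | 0.005 / 0.145 / 5.6% | 0.006 / 0.145 / 5.0% | 0.006 / 0.143 / 5.4% |
| No effect; level and change; differential | 0.059 / 0.149 / 7.2% | 0.035 / 0.148 / 5.6% | 0.001 / 0.147 / 5.1% |
| d = 0.40; level only; equal dropout | 0.402 / 0.143 / 78.5% | 0.402 / 0.143 / 78.7% | 0.402 / 0.143 / 79.4% |
| d = 0.40; level and change; equal dropout | 0.407 / 0.145 / 80.2% | 0.407 / 0.145 / 79.9% | 0.407 / 0.143 / 80.9% |
| d = 0.40; level and change; differential | 0.454 / 0.148 / 85.4% | 0.429 / 0.148 / 81.8% | 0.394 / 0.147 / 75.5% |

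Monte Carlo error is √(0.8 × 0.2/800) = 1.4 points for a power near 80% and √(0.05 × 0.95/800) = 0.8 points for a size near 5%. Three readings follow. Main effects alone leave the standard error unchanged to within 0.001. With equal dropout by arm no bias is visible, even when ECOG predicts both dropout and change. Bias appears only in the differential case, and only the strata-by-time terms remove it. The higher rejection rate without strata in the last row reflects that bias, not better power.

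**The case against.** The strongest case against is that nothing here is invalid. Stratification exists to balance the arms, and it does so whether or not the factors are modelled. A reader might infer that leaving them out wastes the stratification; that does not follow. A reader might also compute several points of lost power by assuming that the strata explain part of the variance of the 3-month score. That calculation belongs to a follow-up-only or baseline-adjusted comparison. The planned test is an interaction against baseline, where stable stratum differences cancel. Both objections stand.

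It is also fair that the documents nowhere say age or ECOG predicts dropout. The pilot statement about medical attrition makes this reasonable for ECOG and says nothing about age. Likelihood estimation already conditions on observed baseline and 2-week scores, and no section suggests the differential dropout that produced bias above. Nor do the documents give a reason why patient age or ECOG should predict change in caregiver burden, the second primary outcome. These limits hold the size of the point down.

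Less persuasive is the argument that a condensed article leaves such matters to the full plan. That is fair for the use of the dropout regression, which is not counted here. But the article does list the fixed effects and does state a covariate rule, and together they make adjustment for the strata unlikely. The moderator analyses in section 3.6 might involve age or ECOG, but they are exploratory and leave the Aim 1 and Aim 2 tests unchanged.

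**Conclusion.** The point holds as a modest, nearly free improvement. The listed Aim 1 and Aim 2 models omit both stratification factors, and section 3.1.2 is unlikely to bring them in. The primary test is not invalidated: without the strata it is valid or slightly conservative. The likely precision gain is small, at about one point of power or less in the simulation and up to about four points in the closed-form calculation if the strata explained 10% of the variance of change.

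The missing-data argument is the better reason to act, but it is conditional. Bias of about 0.06 SD, with type I error near 7%, needs both ECOG-related dropout that differs between arms and an effect of ECOG on change, at the strong values assumed above. The documents support neither a claim that such bias is expected nor a claim that age and ECOG are established predictors of dropout.

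**What to change.** In the Aim 1 and Aim 2 models, prespecify age group and ECOG group, coded as used for randomization, as fixed effects, each with its interaction with time. The interactions are the part that matters, because main effects alone barely touch the tested contrast. State that these terms enter whatever the baseline comparison in section 3.1.2 shows.

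The cost is wording and six parameters per single-role model: two main effects plus two factors × two time dummies. In the models for outcomes reported by both patient and caregiver it is twelve if the terms may differ by social role. Both variables are already collected (sections 2.3 and 2.4, Table 2), and the data analysts are blinded under section 2.4, so the change can be made without knowledge of results.
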